#### Statistical analysis

The analysis of the primary outcome involves the measurement of LAIV viral load over time. The LAIV load at different time points will be analysed in two ways:

The viral load will be summarised using the number, mean, geometric mean, SD, median, minimum and maximum at each time point. Log-transformed value will be analysed using a generalised estimating equation model, in which treatment, time and the interaction between treatment and time as independent factors after taking the correlation of participants into account. An exchangeable covariance structure will be used. The geometric mean ratio between groups together with their 95% CIs at each time point will be derived. If the interaction effect is non-significant, the interaction term will be dropped and the model refit, including only time and treatment fixed effects.The area under the curve (AUC) of LAIV will be calculated by the trapezoidal rule from log10+1 transformed LAIV load results. The AUC will be summarised using the above descriptive statistics, and the log AUC will be analysed using a generalised linear model with a single factor of treatment. The geometric mean ratio between groups, together with their 95% CIs, will be derived.

For secondary and exploratory outcomes, the immune response data are expected to be highly skewed, and the data will be log-transformed prior to analysis. The geometric mean concentration and associated 95% CI will be summarised by computing the anti-log of the mean of the log-transformed data.

Continuous variables such as LAIV viral load and AUC over time will be summarised according to the number of subjects with non-missing data (n), mean, SD, median, minimum and maximum. Categorical variables such as symptoms and serious adverse events (SAEs) will be summarised according to the absolute frequency and percentage of subjects (%) in each category level. The denominator for the percentages is the number of subjects vaccinated with LAIV with data available, unless noted otherwise.

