## Methods and analysis

### Study design and setting

This is a single-site observational study that will enrol up to 40 children over two influenza seasons (September 2024 to February 2025 and September 2025 to February 2026) who are eligible for vaccination with LAIV as part of the National Vaccination Schedule. Children will be visited at home at enrolment and receive the LAIV vaccine as well as 28 days later for a follow-up visit by the clinical team, such that sample collection will be completed in February 2026. Recruitment of study participants will concentrate on Oxfordshire, England, and the surrounding areas to allow the timely transfer of biological samples to the laboratory. Parents will collect nasal lining fluid and saliva samples on days 1, 2, 3, 4, 6, 9, 14 and 21 (figure 1) following home sampling procedures demonstrated at visit 1 (V1) and in online supplemental material 2. Parents/guardians will also complete a daily symptom diary.

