### Microbiological measurements

Viral load will be measured from nasal mucosal lining fluid (nasosorption sample) and salivary samples from V1, home samples and V2 through reverse transcription quantitative polymerase chain reaction (RT-qPCR). Detection of pneumococcus, other respiratory bacteria and common respiratory viruses will be assessed by microfluidic qPCR.

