#### Per-protocol population

For all objectives, analysis will only be carried out on those participants who receive the LAIV appropriately and who are part of the per-protocol population. For the primary outcome (LAIV viral load over time), the per-protocol population is defined as producing a nasal fluid sample at two or more time points prior to D9 post vaccination. For secondary outcomes, the per-protocol population is defined as having provided two blood samples, two home samples prior to D9 and at least the second nasal cell sample.

Exploratory end points will be analysed in the following populations: participants who have provided at least one nasal cell and blood sample and at least one post-vaccination nasorption sample. For some of the analyses, such as gene expression, a subset of participants will be selected for analysis based on clinical outcomes and availability of samples for the desired time points.

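### The viral-load AUC is logged twice, so its ratio is not a ratio of viral load and cannot be computed for a child with no detectable virus

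*Protocol article*

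**What the plan says.** The Statistical analysis section sets out two analyses of LAIV viral load over time.

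- **Repeated measures.** "Log-transformed value will be analysed using a generalised estimating equation model", and from it "The geometric mean ratio between groups together with their 95% CIs at each time point will be derived". No base, offset or detection-limit rule is given for this log.
- **AUC.** "The area under the curve (AUC) of LAIV will be calculated by the trapezoidal rule from log10+1 transformed LAIV load results". The AUC is to be summarised with the same statistics as the daily loads, which include a geometric mean. Then "the log AUC will be analysed using a generalised linear model with a single factor of treatment", and "The geometric mean ratio between groups, together with their 95% CIs, will be derived".

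On sampling, the Study design and setting section says: "Parents will collect nasal lining fluid and saliva samples on days 1, 2, 3, 4, 6, 9, 14 and 21". The Microbiological measurements section adds the home-visit samples at V1 (day 0, taken before vaccination) and V2 (day 28).

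On who is analysed for the primary outcome, the Per-protocol population section says: "the per-protocol population is defined as producing a nasal fluid sample at two or more time points prior to D9 post vaccination". Membership depends on samples given, not on virus being found. Table 1 makes the primary objective strain-specific.

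**The concern.** An AUC of log10 loads is already on a log scale. Logging it again and back-transforming gives the ratio of two log-scale areas. That number has no fixed relation to the amount of virus, yet it carries the same label, geometric mean ratio, as the GEE result, where the label does mean a fold difference in load. The two primary analyses would be reported under one name on scales that cannot be compared.

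The +1 in the AUC transform keeps undetectable samples in the calculation as zeros. The second log brings the problem back at the level of the child: someone negative throughout for a strain has an AUC of 0, and the log of 0 does not exist. Failing to shed is itself a result in a study of mucosal response. Omitting those children would turn the AUC analysis into a description of shedders only.

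**Working it through.** **1. The article's own figure.** The article states no viral load or AUC value. Its only relevant figure is the number expected for the primary analysis: 40 × 0.75 = 30 children, which agrees with the Sample size section.

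**2. Inputs for the AUC check.** Days 0, 1, 2, 3, 4, 6, 9, 14, 21 and 28 come from the article. The following are assumptions: all ten days enter the AUC, the transform is log10(load + 1), and loads follow one of two profiles. The flat profile is 0 on day 0 and a constant load L afterwards. The peaked profile is peak load × (0, 0.1, 1, 1, 0.5, 0.1, 0.01, 0, 0, 0).

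**3. Formula.** AUC = Σ (yᵢ + yᵢ₊₁)/2 × (tᵢ₊₁ − tᵢ), with y = log10(load + 1). For the flat profile this reduces to log10(L + 1) × (0.5 + 27) = 27.5 × log10(L + 1).

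**4. A second child with ten times the load at every time point.** The second log and its back-transformation return the ratio of the two AUCs.

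| Profile | Lower load (L or peak) | AUC, lower | AUC, tenfold higher | Ratio from log AUC | Ratio of raw-load AUCs |
|---|---|---|---|---|---|
| Flat | 10² | 55.12 | 82.51 | 1.50 | 10.0 |
| Flat | 10³ | 82.51 | 110.0 | 1.33 | 10.0 |
| Flat | 10⁵ | 137.5 | 165.0 | 1.20 | 10.0 |
| Peaked | 10² | 11.42 | 21.23 | 1.86 | 10.0 |
| Peaked | 10³ | 21.23 | 32.07 | 1.51 | 10.0 |
| Peaked | 10⁵ | 43.05 | 54.05 | 1.26 | 10.0 |

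The same tenfold difference gives 1.20 to 1.86.

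**5. A hundredfold difference.** Take log10 loads of 0, 3, 4, 4, 3.5, 2 on days 0 to 6 and no virus from day 9. The areas of the successive intervals are 1.5 + 3.5 + 4 + 3.75 + 5.5 + 3 = 21.25 (the +1 changes this only in the second decimal). With every positive load multiplied by 100 they are 2.5 + 5.5 + 6 + 5.75 + 9.5 + 6 = 35.25. The ratio is 35.25/21.25 = 1.66, which lies inside the range that a tenfold difference produced.

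**6. The child with no virus.** Each y = log10(0 + 1) = 0, so AUC = 0 and log(AUC) is minus infinity. The geometric mean of any set containing this AUC also fails. If log10+1 were read literally as log10(load) + 1, a single zero sample would already be undefined.

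**7. Effect of leaving such children out.** Let p be the share never positive for a strain. The article gives no p. The mean AUC of shedders exceeds the mean over all children by 1/(1 − p).

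| Assumed p | Children lost out of 30 | Shedders' mean ÷ mean of all |
|---|---|---|
| 10% | 3 | 1.11 |
| 20% | 6 | 1.25 |
| 40% | 12 | 1.67 |

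In an assumed comparison with equal shedding among positives and 10% against 40% never positive, the ratio of mean AUCs over all children is 0.60/0.90 = 0.67. Among shedders only it is 1.00.

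**8. The AUC without the second log.** For the peaked profile with lower peak 10³, (32.07 − 21.23)/28 = 0.387 log10 per day, and 10^0.387 is about 2.4. For the flat profile, 27.5/28 = 0.982, about 9.6-fold. A mean difference in this AUC is well defined and keeps zeros, but it is not a fold difference in load when both children have negative days.

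**The case against.** Several things can fairly be said for the plan.

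- A reader might infer that the GEE ratio also fails to measure viral load. It does not fail: the GEE logs the load once, and a back-transformed difference of single logs recovers 10.0 for a tenfold difference.
- A reader might also infer that undetectable samples are dropped from the GEE. The article does not say so. It says only that values are log-transformed, and the planned geometric mean at each time point presupposes some rule for undetectable results. Such a rule commonly sits in an analysis plan or laboratory document that is not shown. The Sample size section promises to use all available data.
- Single negative samples stay in the AUC as zeros. Only a child negative throughout is affected, and the article does not say how many to expect.
- The AUC is also to be summarised by mean, SD, median, minimum and maximum. These keep zeros and need no second log.
- The study is exploratory and describes one cohort, all given LAIV. The treatment groups named in both models are not defined, so neither ratio has a stated contrast. That is a separate matter, but it means that no particular comparison can be said to be understated.
- Part of the compression comes from integrating log loads over shared negative days, so removing the second log does not restore a fold difference (step 8).

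All of this stands, and it confines the point to the AUC. It does not rescue the log AUC. The double log is written out, not left to another document. The geometric mean of the AUC fails on one zero even in a single cohort.

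**Conclusion.** The AUC analysis is wrong as written. Its geometric mean ratio compares log-scale areas, and under the assumed profiles a tenfold load difference appears as about 1.2 to 1.9. The log AUC and the geometric mean of the AUC are undefined for any child with no detectable virus for a strain at any time point, although the per-protocol definition admits that child.

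That the ratio is not a viral-load ratio and that a zero AUC has no log follow from the stated steps, reading the transform as log10(load + 1). The sizes rest on assumed loads and curve shapes, and the number of children affected is unknown. The conclusion does not extend to the GEE, for which the article supports neither an uninterpretable ratio nor the exclusion of undetectable samples.

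**What to change.** 1. Write the transform without ambiguity, as log10(copies + 1) or as a stated detection-limit substitution.
2. Choose one AUC analysis:
   - analyse the AUC of log loads without a second log, as a mean or mean difference with 95% CI in log10-copy-days, keeping zeros and not calling it a fold difference in viral load; or
   - if a fold ratio of exposure is wanted, compute the AUC on raw loads and log it once, with a stated rule for zeros.
3. Drop the geometric mean of the log-load AUC, or state how zero AUCs enter it.
4. Use the same rule for undetectable values in the GEE and the per-day geometric means.
5. Report the proportion of children with detectable virus at each day.

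The cost is a change of wording before analysis, with no extra samples or data. The drawback of the first option is that the AUC is reported in log10-copy-days and not as a ratio.

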### Public and patient involvement

For this study, input was sought from the Oxford Vaccine Centre’s Patient and Public Involvement and Engagement (PPIE) group. A focus group involving three PPIE members was convened to discuss the study’s design and objectives. The group provided feedback on participant-facing materials, including information sheets, consent forms and recruitment documents, which was incorporated into the final versions. In addition, PPIE members contributed suggestions on recruitment approaches and advised on strategies for sharing study findings with the broader community.

## Ethics and dissemination

### Ethical and safety considerations

The study will be conducted in accordance with the current approved protocol, Good Clinical Practice guidelines, relevant regulations, the Declaration of Helsinki and local standard operating procedures. A risk assessment and monitoring plan has been prepared and will be reviewed throughout the study. Approved and relevant Standard Operating Procedures (SOPs) will be used at all clinical and laboratory sites. Ethical approval for this study has been obtained from the South Central - Hampshire B Research Ethics Committee and Health Research Authority on 12 August 2024; REC reference: 24/SC/0251. Parental informed consent will be sought by trained researchers prior to any study intervention. The university has a specialist insurance policy in place which will operate in the event of any participant suffering harm because of their involvement in research. The Strengthening the Reporting of Observational Studies in Epidemiology (STROBE) guideline^12^ was used in the development of this manuscript and the STROBE reporting checklist^13^ is included in online supplemental material 7.

### Risks

The general risks to participants from this study are very low. Participants will be counselled for risks from LAIV, including coryzal symptoms, anaphylaxis and wheeze, as well as pain and bleeding or bruising from venepuncture and nasal sampling. Potential participants at risk of more severe side effects will be excluded as per Box 1. Participants have access to a healthcare professional 24/7 in the event of illness throughout the study.

### Safety reporting

As this study is using LAIV in its licensed way, and all study procedures are considered low risk, it is not intended to report on adverse events (AEs) related to the LAIV. However, any suspected SAEs (defined as any AE that results in death, is life-threatening and requires hospitalisation or prolongation of existing hospitalisation, significant disability/incapacity or congenital anomaly/birth defects) will be assessed for relatedness and reported to the sponsor within 24 hours of notification. Reports of related and unexpected SAEs are submitted to the Health Research Authority (HRA) within 15 working days of the chief investigator becoming aware of the event.

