Home sampling will occur on days 1, 2, 3, 4, 6, 9, 14 and 21 post vaccination. Participants’ parents will be taught the technique for collecting SAM strips and salivary samples at visit 1 (V1) and instructed on labelling and storage of the samples in their own freezer until visit 2 (V2). Home samples will be collected at V2 onto dry ice before being processed at the laboratory. A temperature monitor and container for the storage of home samples will be provided by the study team. Temperature data will be evaluated for temperature deviations which may occur during storage in the home freezer following their collection at V2.

Symptom diaries will be issued to parents daily from the day of vaccination through to completion of V2. This will be issued as a Research Elctronic Data Capture (REDCap) survey sent via email, and it will collect information on the participant’s highest axillary temperature (on a thermometer given at V1), the presence and severity of any coryzal symptoms, altered feeding habits, diarrhoea, vomiting, irritability and drowsiness. The severity of each symptom will be graded by parents as per table 2. Any new medication or the need to seek medical attention will also be recorded. These data allow the detection of potential symptomatic intercurrent illness following the vaccination, which may change the interpretation of the data from collected samples. In case of issues completing the online diary, a paper backup diary is provided (online supplemental material 6).

**Table 2 T2:** Symptom diary grading and description

None	No significant symptoms
Mild	Some symptoms, but no effect on usual activity
Moderate	Notable symptoms with some effect on normal activity
Severe	Symptoms that prevent normal activity

Upon completion of the V2, or following participant withdrawal, an optional REDCap end-of-study survey will be emailed to parents. Given that home SAM strip and salivary sampling are relatively new techniques, this survey will help to evaluate the acceptability of this, and the other study activities undertaken for parents and participants.

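### As printed, the SAE definition joins life-threatening and hospitalisation with 'and', so read literally either one alone is not an SAE

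*Protocol article*

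**What the plan says.** The protocol article's Safety reporting section states that "it is not intended to report on adverse events (AEs) related to the LAIV". The exception is suspected SAEs. After a first criterion for fatal events, the definition goes on to say that an SAE "is life-threatening and requires hospitalisation or prolongation of existing hospitalisation, significant disability/incapacity or congenital anomaly/birth defects". This is the only SAE definition in the article.

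Three things hang on it:

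- Suspected SAEs "will be assessed for relatedness and reported to the sponsor within 24 hours of notification".
- A second deadline covers onward reporting to the regulator of health research: "Reports of related and unexpected SAEs are submitted to the Health Research Authority (HRA) within 15 working days".
- The Statistical analysis section summarises SAEs, like symptoms, as frequencies and percentages. The denominator is children vaccinated with LAIV who have data available.

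Separately, the Sample collection section gives parents a daily symptom diary up to the second visit. In it, "Any new medication or the need to seek medical attention will also be recorded". The stated purpose is that "These data allow the detection of potential symptomatic intercurrent illness following the vaccination".

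The Risks section says families are counselled on "risks from LAIV, including coryzal symptoms, anaphylaxis and wheeze".

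**The concern.** Seriousness criteria are normally alternatives: meeting any one is enough. Here an 'and' sits between the life-threatening criterion and the hospitalisation criterion, which turns two sufficient conditions into one joint condition.

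In a study that reports all adverse events, an event that missed the SAE definition would still be reported as an ordinary adverse event. This study deliberately has no such second tier for vaccine-related events. The SAE definition is therefore the only gate to relatedness assessment and to reporting to the sponsor and the Health Research Authority. An error in the gate removes the event from the reporting pathway rather than downgrading it.

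**Working it through.** There is no figure to reproduce. The check is a literal reading of the connectors, followed by a search of the article for anything that corrects them.

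**Step 1: parse the sentence.** One comma follows the death criterion and another precedes the disability criterion. Between them is a single list item in which 'and' ties life-threatening to requiring hospitalisation or its prolongation.

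**Step 2: apply that reading, and the reading with separate criteria, to each kind of event.** Each row assumes that no other criterion is met.

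| Event | SAE as printed (literal) | SAE if criteria stand alone |
|---|---|---|
| Death | yes | yes |
| Life-threatening, admitted | yes | yes |
| Life-threatening, not admitted | **no** | yes |
| Admitted, not life-threatening | **no** | yes |
| Existing stay prolonged, not life-threatening | **unclear** | yes |
| Significant disability or incapacity | yes | yes |
| Congenital anomaly or birth defect | yes | yes |

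The prolongation row is unclear because the phrase can be governed by 'requires', and so fall under the joint condition, or be separated from it by the 'or'.

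**Step 3: trace the consequences for the two 'no' rows.**

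- Relatedness assessment and the 24-hour sponsor report apply to suspected SAEs, so neither is triggered.
- The report to the Health Research Authority applies to SAEs that are related and unexpected, so it cannot be triggered either. Under the separated definition it would follow only for events that are also related and unexpected.
- The event is not counted in the SAE frequencies.

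The risks that the article itself names illustrate both rows: an admission for wheeze that is not life-threatening, and anaphylaxis treated without admission.

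**Step 4: look for a correction elsewhere.** The article has no second definition. The diary collects symptoms, new medication and need for medical attention, and symptoms are tabulated, so traces of such an event could appear in the data. But the diary serves the interpretation of samples, and no route from it to safety reporting is described.

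**Step 5: scale.** With the planned maximum of 40 children all vaccinated and with data, one event is 1/40 = 2.5%. This shows only how much one child weighs in the table. The article gives no expected rate of admissions, so the number affected cannot be estimated.

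**The case against.** The strongest reply is that this is a badly written list and not a rule. Three verbs follow one another (results, is, requires), and the 'and' can be read as closing that series. Taken strictly, that reading would make death a requirement too, which is absurd, so a reader would recognise a list of alternatives with the wrong connector. The rest of the sentence is out of parallel in the same way, since 'requires' seems to govern disability as well. The article also says that it follows protocol version 2.0 and that the study is run under the approved protocol, Good Clinical Practice and local procedures. Staff may therefore classify events by wording not shown here.

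Most of this stands as an account of how the error arose, and it makes a slip the likeliest explanation. It does not make the sentence right. An article may leave detail to the full protocol, but this is a definition that it chose to state, and it states it wrongly.

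Two further objections stand in full. Safety is not among the study's objectives, so the viral load, antibody and transcriptome analyses are untouched. And the percentage denominator is already vaccinated children with data, so nothing there needs repair.

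A reader might infer more: that the study chose to exclude ordinary admissions, or that admissions will go unreported and unseen. The documents do not support either. No such choice is stated anywhere, nothing shows how events are classified in practice, suspicion alone is enough to start the assessment, and the diary may show the event.

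**Conclusion.** The printed definition is wrong as written. Followed literally, it leaves out admissions that are not life-threatening and life-threatening events without admission, and these then have no reporting route to the sponsor or the Health Research Authority and no place in the SAE counts.

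The conclusion rests on two things that can be checked in the article: the 'and' in the definition, and the decision not to report other vaccine-related adverse events. It does not rest on any assumption about how many such events will occur, and no rate is claimed.

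It is probably a drafting or condensing slip. Whether it has any effect in practice depends on the wording of the full protocol, which is not shown. It merits correction because it governs safety reporting in young children; it does not threaten the study's scientific analyses.

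**What to change.** Compare the sentence in the Safety reporting section with the SAE definition in the full protocol. If the slip is only in the article, correct the article; if the protocol shares it, amend the protocol as well. Each criterion should stand alone, joined by 'or': death; life-threatening; hospitalisation or its prolongation; disability or incapacity; congenital anomaly or birth defect.

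Count the SAEs summarised under Statistical analysis on that definition, and keep the denominator as it is.

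The cost is a wording change, plus an amendment if the protocol has the same text. No visit, sample or procedure is added.
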